### 2.2. Pilot Study Design

For the pilot study, 30 participants will be recruited to evaluate the feasibility (in terms of acceptability and satisfaction, usability, and uptake) of the IB-CBT program. Inclusion and exclusion criteria, detailed in the following paragraphs, will be the same as for the RCT. Baseline and post-treatment assessments will be conducted using the same methods and scales used in the RCT and described in the following paragraphs. We assume most students will accept the treatment and be satisfied with it. However, some participants may run into technical or access issues, as stated by previous studies [28] (e.g., Wilks et al., 2018).

#### Feasibility Measures

At the end of the pilot, different feasibility aspects will be assessed using the following scales:❖Treatment satisfaction, measured by a modified version of the Client Satisfaction Questionnaire (CSQ-8) [31], an 8-item questionnaire rated on a 4-point Likert scale; and a Visual Analogue Scale (VAS) [32];❖System usability, via completion of a modified version of the System Usability Scale (SUS) [33], which is a 10-item questionnaire rated on a 5-point Likert scale that provides a global measure of subjective usability; and a VAS [32];❖Adherence rates for each lesson and the overall program.

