## Abstract

Despite the widespread prevalence of mental health problems, most psychological distress remains untreated. Internet-based psychological interventions can be an essential tool for increasing treatment availability and accessibility. The main objective of the MindBlooming project is to design and implement an innovative Internet-based multi-approach treatment for university students suffering from psychological or physical problems. The intervention will focus on symptoms of depression, anxiety, sleep problems, self-destructive thoughts, job- and study-related stress and burnout, and chronic pain. It will be based on different approaches, primarily psychoeducation, Cognitive-Behavioral Treatment (CBT), and third-wave CBT. At the end of the treatment, user satisfaction and usability will be assessed. In addition, two further aims will be evaluating the treatment efficacy through a randomized controlled trial and tuning a predictive model through Machine Learning techniques. The intervention consists of a 7-week treatment on two problematic areas according to each students’ personal needs, identified through an initial assessment. Besides the treatment assigned following the initial screening, participants will also be assigned to a different module to improve their relational skills. The treatment, which can be accessed through a mobile app, consists of psychoeducational videos followed by related exercises. We expect MindBlooming to be a remarkable tool for promoting the mental health of university students.

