### Aims and Hypotheses

MindBlooming is a two-year research project with multiple primary goals and related hypotheses. Firstly, we aim to design and implement a new Internet-Based Multi-Approach Intervention (IB-MAI) for university students. The intervention covers a wide range of mental health issues that are relevant within the university student population [11,28] and that are treatable with IBIs [23,25,29]. Furthermore, the intervention is tailored to the individual’s needs. The mental health issues that MindBlooming addresses are depression, anxiety, sleep problems, self-disruptive thoughts, job- and study-related stress and burnout, and chronic pain.

Secondary aims will be: (1) the feasibility assessment of this IB-MAI (in terms of acceptability, satisfaction, usability, and uptake) through a pilot study on a restricted sample; (2) a randomized controlled trial (RCT) to compare the IB-MAI with web-education, as the control condition (CC); and (3) exploratory analysis to tune a predictive model on the collected data adopting Machine Learning techniques.

We hypothesize that: (1) the design and implementation of the IB-MAI treatment will be feasible; (2) the majority of the students will accept and be satisfied with the treatment; (3) the IB-MAI will be superior to the CC on both the primary and secondary outcome measures; and (4) the large amount of collected data will allow the identification of predictors of treatment response and different trajectories in treatment response.

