### 2.6. Outcome Measures

Participants will be screened with a complete online battery to assess their symptoms, including both primary and secondary outcome measures, at pretreatment baseline (T0), after the 7-week IB-MAI treatment, or CC completion (T1), at 12-week follow-up (T2), and 24-week follow-up (T3) (see Figures S1 and S2 for the study design and assessments). Moreover, at pretreatment time (T0), socio-demographic questions are included; these concern marital status, educational qualification, employment status, physical or psychiatric illnesses, and past or current therapies. Questions related to gender and the COVID-19 pandemic are included to investigate the influence of the pandemic on students’ mental health status. These items were drawn up according to the International COVID-19 Suicide Prevention Research Collaboration guidelines [56]. In contrast, those relating to gender were taken from the Williams Institute of the UCLA School of Law for health surveys [57].

Since participants have a timeframe to begin and complete each week of treatment, the overall treatment duration can differ among subjects. Therefore, post-treatment and follow-up time points will be calculated for each participant, starting from the end of the last activity.

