#### 2.6.2. Secondary Outcome Measures

❖Visual Analogue Scales (VAS) for psychological and physical pain (6 items) [32].❖Insomnia Severity Index (ISI) to investigate the impact of insomnia in the last two weeks (7 items) [74].❖Toronto Alexithymia Scale (TAS-20), consisting of 20 items investigating levels of alexithymia [75,76].❖Coping Orientation to the Problems Experienced (COPE-NVI-25) [77,78], consisting of 25 items investigating coping strategies.❖Life Events Checklist (LEC) [79], composed of 16 items investigating the subject’s stressful experiences.❖Reasons for Living Inventory (RFLI) [80], consisting of 48 items investigating the subject’s reasons for living.❖COVID-19-related questions compiled according to the International Association for Suicide Prevention (IASP) guidelines for suicide prevention research [56].

Given the feasibility nature of this study, data on the program’s acceptability will also be collected at post-treatment (T1) through the same measures used in the pilot study and described in the related paragraph.

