### 2.7. Sample Size Calculation

Considering the attrition rate, we will recruit 260 students to obtain 200 study completers. A total of two-hundred participants will allow to detect an effect size of at least d = 0.40, fixing a power (1 − β) of 80%, and an alpha of 0.05 (two-tailed) in a between group comparison (e.g., comparing the two treatments). This sample size is similar to Harrer et al. [25]. The effect size is estimated considering a recent meta-analytic review for Internet-based stress interventions which reports effect sizes ranging between d = 0.32 and d = 0.64 [81].

Frequentist and Bayesian approaches have their own advantages and drawbacks in data analysis. We will adopt both to provide robust evidence to the specific statistical approach.

We conducted a Bayes Factor Design Analysis (BFDA) [82] (i.e., the counterpart of power analysis in the Bayesian world) to estimate the Bayesian analysis sensitivity, given the sample size of 200 people. We simulated 10,000 results, fixing the Bayes Factor (BF) decision boundary at 10, and an estimated effect size for a true H1 equal to d = 0.40. The BFDA simulation was performed for a default prior (i.e., a Cauchy distribution with a scale = 0.707) and an informative prior (i.e., a t distribution with μ = 0.35, df = 3, r = 0.102), considering true H0 (i.e., d = 0) and H1 (d = 0.40). Given those parameters, we estimate to surpass the decision boundary for H1 in 87.8% adopting the default prior and 93.8% of the case adopting the informed prior. In the case of a true H0, the decision boundary is surpassed in 45.5% and 62.2% of the cases adopting the default or the informed prior, respectively. The design is robust to the misleading evidence, showing a false positive evidence rate of 0.002 and 0.006 adopting the default or the informed prior. No false negative evidence has been observed over 10,000 simulations with any of the two priors. In the case of inconclusive evidence, we will increase the sample size until the BF decision boundary is surpassed (BF > 10) in either one of the two directions supporting H1 or H0.

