## 3. Discussion

This paper describes MindBlooming, a new IB-MAI designed to promote mental health in university students, and describes the study protocol, testing its efficacy through a pilot study and a two-arm RCT. The treatment will be compared to a control condition. Participants’ acceptance and usability of the app will also be assessed to identify possible implementation barriers.

A primary limitation of our project might be represented by the treatment dropout level; due to its overall structure and duration, an IB-I such as MindBlooming requires user commitment and the investment of time and resources, which are not always available. Moreover, some common psychological issues were not addressed within the treatment due to their complexity (i.e., eating disorders and substance use disorder). Further limitations concern the assessment phase and the fully automated nature of the treatment. Indeed, only self-report questionnaires are used to identify possible psychological issues and assign modules during the assessment phase. Although this simplifies the procedure, it also makes it more challenging to provide an in-depth assessment. Lastly, the user’s complete autonomy does not make possible to verify whether theoretical sessions of psychoeducation and exercises have been completed.

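### Satisfaction and usability are rated once, after treatment, and so mainly by students who stayed, whereas hypothesis 2 is about the majority of students

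*Protocol article*

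**What the plan says.** Feasibility, including acceptability, satisfaction and usability, is a stated secondary aim. The matching hypothesis is that "the majority of the students will accept and be satisfied with the treatment" (Aims and Hypotheses).

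The timing of the ratings is stated in three places:
- Abstract: "At the end of the treatment, user satisfaction and usability will be assessed".
- Feasibility Measures, under Section 2.2: "At the end of the pilot, different feasibility aspects will be assessed using the following scales". The list covers CSQ-8 with a VAS, SUS with a VAS, and adherence for each lesson and overall.
- Section 2.6.2, for the RCT: acceptability data "will also be collected at post-treatment (T1) through the same measures used in the pilot study".

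Section 2.6 places T1 "after the 7-week IB-MAI treatment, or CC completion (T1"). Section 2.4 removes from the study students who do not keep to the weekly deadlines. Section 2.7 states "we will recruit 260 students to obtain 200 study completers", and the Discussion concedes: "A primary limitation of our project might be represented by the treatment dropout level". No earlier rating and no rating at the point of leaving is described.

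**The concern.** The hypothesis concerns students in general, but the only rating comes after the programme. A student who finds the app burdensome or hard to use, falls behind and is excluded has no stated occasion to say so. If such students are less satisfied than those who stay, the share satisfied among respondents overstates the share among all who started. The hypothesis could then be declared met when fewer than half of the starters were satisfied.

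This matters most in the pilot, which is meant to find usability and access problems before 260 students are recruited. Section 2.2 itself expects some technical or access issues. The efficacy comparison in the RCT is not affected.

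**Working it through.** **The plan's own figure.** The article gives no number for the satisfaction hypothesis, so the figure to reproduce is the sample size in Section 2.7 (d = 0.40, 80% power, two-sided alpha 0.05).
- Normal approximation: 2 × (1.960 + 0.842)² / 0.40² = 98.1, rounded up to 99 per arm, 198 in total.
- Based on the t distribution: 99.1 per arm. Power with 100 per arm is 80.4%.

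The 200 completers reproduce and are not in dispute. The implied attrition is a = 60/260 = 23.1%.

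**Inputs for the check**
- a = 23.1%, from Section 2.7, for the RCT as a whole. Applying it to the pilot and to the IB-MAI arm at T1 is an assumption.
- Completers: 30 × 200/260 = 23 in the pilot; 130 × 200/260 = 100 in the IB-MAI arm.
- Satisfied share among leavers, L: not in the documents. Assumed values are 0%, 20%, 30% and 40%.
- Some cut that divides satisfied from not satisfied is taken as given.

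**Formula.** With C the satisfied share among completers, the share among starters is (1 − a) × C + a × L. It reaches 50% when C = (0.5 − a × L) / (1 − a). For C between 50% and this value, most completers are satisfied but most starters are not.

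**Results at a = 23.1%**

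| Leavers satisfied (assumed) | Break-even C | Range in which the two disagree |
|---|---|---|
| 0% | 0.500 / 0.769 = 65.0% | 50% to 65% |
| 20% | (0.500 − 0.046) / 0.769 = 59.0% | 50% to 59% |
| 30% | (0.500 − 0.069) / 0.769 = 56.0% | 50% to 56% |
| 40% | (0.500 − 0.092) / 0.769 = 53.0% | 50% to 53% |
| same as completers | 50% | none |

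**Other attrition rates, L = 0.** The break-even is 0.5/0.9 = 55.6% at 10%, 0.5/0.7 = 71.4% at 30%, and 0.5/0.6 = 83.3% at 40%.

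**In whole students, L = 0.** In the pilot, 12 of 23 is 52% of completers but 12 of 30 is 40% of starters. 15 of 23 is 65%, but 15 of 30 is exactly half. A majority of starters needs 16 of 30, which is 16 of 23 = 70% of completers.

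**How likely a misleading majority is**
- L = 0, C = 60%: the share among starters is 0.769 × 60% = 46.2%. The exact binomial chance that more than half of completers report satisfaction is 0.97 for 100 completers and 0.84 for 23.
- L = 20%, C = 55%: the share among starters is 0.769 × 55% + 0.231 × 20% = 46.9%. The chances are 0.82 and 0.69.

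**The case against.** **Nothing says that only completers are rated.** A reader might infer that a student who stops in week 2 certainly never rates the app. The documents do not go that far. The end of the pilot is a study time point, no section confines the scales to completers, and Section 2.6 counts post-treatment time points from each participant's last activity, a date that an early leaver also has. This stands as a limit on wording. The deadline exclusion in Section 2.4, with no later assessment described for those excluded, still makes it the natural reading that most ratings come from stayers.

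**The pilot is not blind to dropout.** A reader might conclude that low acceptance would go unseen. That is not supported: adherence per lesson would show a collapse in week 2, and students can take technical questions to an e-Coach. What is not captured is narrower: the leavers' satisfaction, their usability rating and their reasons.

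**The size is assumed.** The 23.1% covers both RCT arms, and Section 2.7 does not say whether completion means T1 or the 24-week follow-up. Treating every leaver as dissatisfied is the extreme case. The Discussion links dropout to the commitment, time and resources required, and Section 2.4 removes students for lateness alone. This objection stands, which is why the size is given as a range.

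**Denominators belong in an analysis plan.** This stands in part. Their absence from an article is no fault. The single late measurement, however, is something the article fixes.

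**Counting every non-responder as dissatisfied has its own bias.** It can reject a true hypothesis, because it merges lateness and questionnaire non-response with dissatisfaction. This stands, so such a count serves as a bound and not as the main figure.

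**Conclusion.** The point holds in a limited form. The plan measures satisfaction and usability once, after treatment, and removes students who fall behind, so it answers a hypothesis about students in general mainly from those who stayed.

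At 23% attrition, a completer majority is misleading only when completer satisfaction is above 50% and below a limit of 65% at most. That limit falls towards 50% as leavers become more like stayers. These figures rest on carrying the RCT attrition over to the pilot and the IB-MAI arm, and on assumed satisfaction among leavers. The documents do not show that the hypothesis is false or that leavers are dissatisfied. They plan no ratings that would settle the matter either way. Because a secondary feasibility aim is at stake and not the efficacy comparison, this is a worthwhile improvement and not a fatal flaw.

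**What to change.** 1. Trigger the same CSQ-8, SUS and VAS automatically when a student stops or is excluded for a missed deadline, in addition to the rating after treatment. Do this in both the pilot and the IB-MAI arm.
2. Report hypothesis 2 with the number of respondents out of all starters (30 in the pilot; all students randomised to IB-MAI in the RCT). Give the respondents' figure together with a bound that counts non-responders as not satisfied.
3. Claim a majority of students only if it survives that bound. Otherwise state that the finding applies to respondents.

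The app already sends daily and weekly questions and tracks deadlines, so the technical cost is one further prompt. The downsides are a small added questionnaire burden, only partial response among leavers, and a satisfaction figure that may look less favourable.

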### 2.3. RCT Design

This study will be conducted in accordance with the Consolidated Standards Of Reporting Trials (CONSORT) checklist for the RCT design [34]. Participants will be randomly assigned following blind simple randomization procedures when they complete the baseline assessment (randomization sequence under computer control adopting computerized random numbers) to 1 of 2 treatment groups (see Figures S1 and S2 for the study design and assessments). We only keep the 1:1 ratio constraint at the 260th participant, meaning that when one group reaches 130 participants, all the remaining volunteers (up to the total of 260) will be allocated to the other group. Students will be randomized to IB-MAI or CC. Participants in the intervention condition will receive an 8-week unguided IB-MAI program, i.e. MindBlooming. Participants in the CC condition will access websites with information about their specific areas of distress identified at baseline. Participants will be assessed with repeated measures (baseline, 8 weeks, 12 weeks, and 24 weeks). The RCT participants’ flow is presented in Figure 2.

### 2.4. Intervention

MindBlooming is conceived as an Internet-Based Multi-Approach Intervention (IB-MAI) intended to provide psychoeducation and teach new strategies to cope with different psychological problems. We consider MindBlooming to be multi-approach since it integrates different psychotherapeutic strategies such as Cognitive Behavioral Therapy [35], Acceptance and Commitment Therapy [36], Mindfulness-Based Cognitive Therapy (MBCT) [37,38], Mindfulness-Based Stress Reduction (MBSR) [39], and Dialectical Behavioral Therapy [40]. All these interventions are evidence-based and several studies proved their efficacy in treating different psychological conditions (for an overview, see [41] and APA division 12 list of research-supported psychological treatments, https://div12.org/psychological-treatments/, accessed date 29 December 2021). The intervention consists of 6 interactive modules: depression, anxiety, sleep problems, self-disruptive thoughts, job- and study-related stress and burnout, and chronic pain. A total of two modules will be assigned to each participant based on the initial screening and specific requests and preferences. In addition to the assigned treatments based on the initial screening, all participants will receive a separate training to improve their relational and empathy skills: during the 6th week, they will have access to two videos focused on the importance of relationships on our health, social support as a protective factor, social isolation and loneliness as a risk factor, emotion regulation, and empathy. Afterward, they will have access to a set of exercises, including quizzes about social relationships, assertive communication training, DBT [40], and Interpersonal Psychotherapy (IPT) for Depression strategies (which correlate depressive symptomatology to relational problems) [42]. Moreover, during the 7th week of treatment, more contents in the same formats (videos, texts, and quizzes) will be proposed, focusing on emotions and relationships problems related to the specific issues faced in the assigned modules (e.g., problems in relationships in association with depressive symptoms).

Every week for the entire duration of the intervention, participants will have access to one session per module, except for the 6th week, which is dedicated to the treatment of relational problems: regardless of the specific issue (depression or anxiety, etc.), this training deals with relational issues relevant to everyone, hence the importance of transversally proposing it. The modules will be presented as follows:○1st week: module 1 and 2 sessions;○2nd week: module 1 and 2 sessions;○3rd week: module 1 and 2 sessions;○4th week: module 1 and 2 sessions;○5th week: module 1 and 2 sessions;○6th week: relational problems related to difficulties in emotion regulation and empathy deficits session;○7th week: module 1 and 2 sessions about relapse prevention, future planning by reflecting on how to attain goals and implement behavioral changes, orientation, and conclusion.

All online sessions will include psychoeducational videos (brief seminars of 15 min each, with audios and PowerPoint presentations), about epidemiology, explanatory models, risk and protection factors, treatments, and some specific aspects of each psychological issue. Once the videos have been seen, training exercises will be proposed to help participants to integrate the content of the sessions into their daily lives (Figure 3). Contents and approaches used for each module are further presented in Table 1.

Quizzes will be presented during each session, along with the possibility for the participants to reply and insert text. Subsequent sessions will be available only if the previous session, and a minimum of related exercises, is completed within 7 days (+3 days to be flexible in the case of students unable to maintain the pace). Even if the contents are completed before the 7th day from the start, new contents will be available from the 7th day onwards. When a new week of treatment is available, participants have 3 days to start completing the tasks. If the subjects do not respect the deadlines, they will be excluded from the study. Participants also have access to a list of available supplementary resources.

For the entire duration of the treatment, participants must answer daily and weekly questions related to each of the two treatment modules they are individually following to constantly monitor the progress of some key variables. The sixth week is an exception, as daily and weekly questions will also address relational issues. Answers are saved and shown to participants on a calendar to follow-up changes over time. Moreover, participants are informed that they can contact an e-Coach for technical questions and concerns or emotional crisis at any time during the intervention.

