### 2.1. Participants and Recruitment

University students aged between 18 and 29 will be invited to participate; to be included, they must declare to have experienced at least mild- or moderate-intensity forms of mental health symptoms (no specific diagnostic screening will be performed in this phase), and they must not currently be in psychotherapy or start psychotherapy during the entire duration of the treatment. Participants are also required to have a phone based on Android or iOS operating systems and an Internet connection. Exclusion criteria include the inability to communicate in Italian.

Participants will be recruited through social networks (e.g., Facebook and Instagram), students’ WhatsApp groups (to include students not using the mentioned social networks, thus avoiding selection biases), and the Sona System recruitment platform made available by the University of Milan-Bicocca. Moreover, to further encourage participation, posters will be placed in local universities. In this phase they will receive preliminary information. Then, through a web link, they will be redirected to a specific landing page with more detailed information about the mobile app. On this web page, participants will be redirected to the proper marketplace (Apple Store and Google Play) to download the app on their smartphones. If possible, European Credit Transfer and Accumulation System (ECTS) credits will be awarded to participants. Once their eligibility has been verified and they have signed an online informed consent form, students interested in participating will be included in the study. We will collect the information concerning the diverse participants’ recruitment channels to ensure that there is no difference in baseline data among different recruitment channels. The same standards for data collection will be applied through different channels.

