### 2.5. Control Condition

For each participant, the CC consists of indications to websites specifically focused on the different psychological conditions (depression, anxiety, sleep problems, self-disruptive thoughts, job- and study-related stress and burnout, and chronic pain) they report as areas of distress according to the global screening.

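### Missing a weekly app deadline removes a participant from the study after randomisation, and as written the rule binds only the IB-MAI arm

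*Protocol article*

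**What the plan says.** **Timing of randomisation (section 2.3).** "Participants will be randomly assigned following blind simple randomization procedures when they complete the baseline assessment". Allocation therefore precedes the first app week. The target is 130 per arm: "We only keep the 1:1 ratio constraint at the 260th participant".

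**The deadlines (section 2.4, Intervention).** The next session opens only if the previous one, with a minimum of its exercises, is finished within 7 days plus a 3-day margin. In addition, "When a new week of treatment is available, participants have 3 days to start completing the tasks". The consequence of failing is "If the subjects do not respect the deadlines, they will be excluded from the study". Loss of access to later sessions is covered by its own sentence, so this one goes further.

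**The control arm (section 2.5).** "the CC consists of indications to websites specifically focused on the different psychological conditions". Section 2.6 mentions completion of the control condition but attaches no activity or deadline to it.

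**Sample size and analysis.** Section 2.7: "we will recruit 260 students to obtain 200 study completers". Section 2.8 compares the T0 to T1 changes of the two arms by t-test and its Bayesian counterpart.

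**Assessment timing (section 2.6).** Post-treatment and follow-up dates are counted for each person from the end of that person's last activity.

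**Verifying completion (section 3).** The user's autonomy "does not make possible to verify whether theoretical sessions of psychoeducation and exercises have been completed".

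**The concern.** A participant who falls behind in the app leaves the trial. A control with the same motivation and symptom course has no deadline to miss and stays. The app arm is filtered on behaviour after allocation and the control arm is not, so the two groups at T1 are no longer comparable by design. Any link between keeping up with the app and improving anyway is read as a treatment effect.

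What is at stake is hypothesis 3, superiority of the IB-MAI over control. The damage is hard to undo: if exclusion means that T1, T2 and T3 are not collected, no later choice of analysis set can recover those outcomes. The rule may also be triggered often, because section 3 itself names dropout as a primary limitation.

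**Working it through.** **1. The plan's own figures.** Inputs from section 2.7: d = 0.40, power 80%, two-sided alpha 0.05, 260 recruited, 200 completers.

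- Normal formula: n per arm = 2(1.960 + 0.842)² / 0.40² = 98.1, so 99 per arm. The t-based solution is 99.08, so 100 per arm and 200 in total.
- Power at 100 vs 100 is 80.4% (t).
- Implied attrition: 60/260 = 23.1%; 200/(1 − 0.231) = 260.

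The stated 200 and 260 reproduce. The split of the 60 losses by arm is not given.

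**2. Model for the rule, with no true effect.** Assumptions, none from the document: adherence and improvement are bivariate normal with correlation r; the least adherent share q of the 130 app users is removed; all 130 controls are kept. The expected spurious difference in SD units is

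bias = r × φ(z_q) / (1 − q), where z_q is the q-quantile of the standard normal distribution.

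- q = 60/260 = 0.231: φ(−0.736) = 0.304; 0.304/0.769 = 0.395, so bias = 0.395r.
- q = 60/130 = 0.462 (all planned losses in the app arm): φ(−0.097) = 0.397; 0.397/0.538 = 0.737, so bias = 0.737r.

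**3. Rejection rate.** Two-sided t-test at 0.05, 10,000 simulated trials per scenario:

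| Kept (app vs control) | r | Spurious d | Rejection |
|---|---|---|---|
| 100 vs 130 | 0 | 0 | 4.9% |
| 100 vs 130 | 0.1 | 0.04 | 6.2% |
| 100 vs 130 | 0.2 | 0.08 | 9.2% |
| 100 vs 130 | 0.3 | 0.12 | 14.6% |
| 70 vs 130 | 0 | 0 | 4.8% |
| 70 vs 130 | 0.1 | 0.07 | 8.3% |
| 70 vs 130 | 0.2 | 0.15 | 17.2% |
| 70 vs 130 | 0.3 | 0.22 | 31.7% |

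A check with the noncentral t-distribution gives 6.0%, 9.1% and 14.4% for r = 0.1, 0.2 and 0.3 at 100 vs 130, and 7.9%, 16.8% and 31.8% at 70 vs 130.

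**4. Power.** At 70 vs 130, power for d = 0.40 is 76.6%, against 80.4% at 100 vs 100. Unequal arms cost little; the bias is the problem.

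**5. If everyone is followed.** At 130 vs 130 with complete data, power for d = 0.40 is 89.5%. This does not allow for a smaller average effect once non-adherent users count.

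**The case against.** **The one-arm reading rests on silence.** Section 2.6 refers to completion of the control condition, and the flow figure is not shown. This limits the claim to what is written: no control task or deadline is described. It does not rescue the rule, since a missed deadline needs a deadline to miss.

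**A separate analysis plan may specify analysis as randomised, and section 2.3 commits to CONSORT.** The choice of analysis set can indeed be left to such a plan. The exclusion sentence cannot, because it decides whether outcomes are collected at all.

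**The direction of bias is assumed.** This stands. A reader might infer that the rule must favour the app. Students who feel better early may stop using it, making r negative and turning the bias against the app. If controls are also lost through low motivation, the bias shrinks.

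**Some stronger readings go beyond the text.**

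- That the comparison is adherent users against everyone in control: controls can still be lost for other reasons, so it is controls who return T1 data.
- That the psychotherapy clause in section 2.1 ("they must not currently be in psychotherapy or start psychotherapy during the entire duration of the treatment") is a second removal rule: it is an eligibility condition, and nothing says that a participant who starts therapy is removed.
- That the rule cannot be operated because completion cannot be verified: section 2.4 describes quizzes, text entry and gated sessions, so a deadline could be tied to logged actions. The two sections need reconciling, no more.
- That false-positive rates of 20% or more are the expected result: they need heavier exclusion or a stronger correlation than the plan's overall attrition with a modest r.

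**Conclusion.** The point holds, and the sentence should be changed before the RCT runs. The protocol states an affirmative rule that removes randomised participants for conduct that, as described, only the app arm can show. This is an error in what is written and not a missing detail.

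The figures are a range and not an estimate. At the plan's overall attrition applied to the app arm, r from 0 to 0.3 yields 0 to 0.12 SD, up to about 30% of the planned d (0.12/0.40), and rejection of about 5% to 14% against a nominal 5%. With all 60 losses in the app arm, r from 0.1 to 0.3 yields 0.07 to 0.22 SD and about 8% to 32%. At r = 0 there is no inflation. The figures rest on an unstated r, an assumed split of losses, and full retention of controls. What does not depend on r is that the comparison loses the protection of randomisation.

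**What to change.** - **Section 2.4:** separate app access from study membership. How access is managed after a missed deadline is for the investigators. The participant stays in the trial, is sent T1, T2 and T3, and is analysed in the arm assigned. Label any completer analysis as a sensitivity analysis.
- **Section 2.6:** time T1 to T3 from randomisation, on the same schedule in both arms, in place of the last-activity rule. Otherwise someone who stops in week 2 would be due T1 at about week 2, and the first change would not work. Section 2.3 already lists assessments at 8, 12 and 24 weeks, so the two sections should be aligned.
- **Section 2.7:** restate the 200 as participants with a T1 assessment, out of 260 randomised.
- **Sections 2.4 and 3:** reconcile the completion-based deadline with the statement that completion cannot be verified.

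The cost is protocol wording, reminders to people who have stopped using the app, and possibly a smaller estimated effect because non-adherers count. Against that, every non-adherer who returns T1 adds to the analysed sample.
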